**Removal of CPAP/ EXIT from CPAP**:

CPAP will removed if following criteria are satisfied:

1. CPAP of 4 cm of H_2_O with FiO_2_<30%
2. Hemodynamically stable
3. Good respiratory efforts
4. Apnea and bradycardia free for last 24 hours

**Table 1 :**Nasal Injury Assessment score chart **^(21)^**

| **Tip of Nose** | 0=Normal  1= Red  2= Red + indent  3=Red/indent/skin breakdown  4=As above +tissue loss |
| --- | --- |
| **Nasal Septum** | 0=Normal  1=Red  2=Red + indent  3=Red / indent / skin breakdown  4=as above + tissue loss |
| **Nostrils** | 0=Normal  1= Enlarged  2= Enlarged and prong shape  3=Red, bleeding  4=As above + skin breakdown |
| **Nose Shape** | 0= Normal  1=Pushed up/back but normal  2=Pushed up and shortened. No normal orientation when prongs removed. |
| **Bridge of the nose** | 0=Normal  1= Red  2= Red + indent  3=Red/indent/skin breakdown  4=As above +tissue loss |
| **Upper lip** | 0=Normal  1= Red  2= Red + indent  3=Red/indent/skin breakdown  4=As above +tissue loss |

**Scoring:**

0= No injury

1-4= mild injury

5-6= moderate injury

≥7= severe injury

**Flow of study**

Intervention

Outcome

Screen for eligibility (n=)

Number of neonates enrolled

Initial Mask group

Initial Prongs group

Continuous Mask group

Interface

rotation

group

Continuous Prong

group

Interface

rotation

group

Number of neonates excluded =

Causes:

Primary and secondary outcomes

Enrollment

Randomization

**First Randomization**

**Second Randomization**

**Statistical analysis**

Categorical outcome variables will be analysed by Chi square test with continuity correction or Fisher’s exact test. Normal distributed independent variables will be compared by repeated measures ANOVA test whereas a non-parametric test (Mann-Whitney U) will be used for variables with a skewed distribution. An Intention to treat analysis will be done (ITT). All analysis will be done using IBM SPSS version 21 and Microsoft Excel. A P value of less than 0.05 will be considered significant.

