**MATERIAL & METHODS**

Study site:

NICU, Fernandez Hospital, Hyderabad.

Study design:

A Prospective, Randomized, Comparative study.

Sample size with justification:

Assuming an incidence of nasal injury of 50% among the control group at the removal of CPAP from literature review and previous study from our center^(2-6)^. Assuming three group comparisons with an effect size of 30% with 80% power, alpha error of 5% the sample size calculated is 48 in each group and assuming an attrition rate of 10% we need 55 neonates in each group. Sample size was estimated by using Compare k Proportions: 1- way ANOVA Pairwise test ([www.powerandsamplesize.com](http://www.powerandsamplesize.com)). We will enroll patients till a minimum of 55 infants are enrolled in each group.

Time frame:

From september 2016 to march 2018.

Study population

Neonates admitted in NICU for respiratory distress

Inclusion criteria

- All inborn neonates <=30 weeks of gestation and
- Developed respiratory distress (presence of at least two out of three signs: tachypnea > 60/min, intercostal retractions, and expiratory grunt) within 6 hours of life.

Exclusion criteria

- Patients who have Perinatal depression (5 minute Apgar score of ≤3),
- Patients with Life threatening congenital malformations such as congenital diaphragmatic hernia, and trachea-esophageal fistula, other malformations that would prevent from establishing CPAP due to the anatomical defect such as Pierre-Robinson syndrome and choanal atresia
- Conditions where CPAP would be contraindicated such as neonates with poor spontaneous respiratory efforts or apnea, worsening shock, suspected or proven persistent pulmonary hypertension of newborn, severe metabolic acidosis (pH<7.2 with base deficit > -10), severe respiratory acidosis (pH<7.2 with PaCO2>55mmHg) and massive pulmonary hemorrhage

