**OUTCOMES MEASURED**

Six hours after the removal of nCPAP, infants will be assessed for nasal injury (Table 1) and digital photographs will be taken that will be reviewed by a senior neonatologist blinded to the study group allocation. Incidence and severity of nasal injury is the primary outcome of the study. Bedside subjective assessment of nasal injury will also be done by one of research assistant and this included; a) dilation of nares, b) columella indentation or excoriation, c) notching on the bridge of nose, d) altered shape of nose and e) redness /indentation/bleeding/excoriation of any area of nose.

The secondary outcomes of the study includes nCPAP failure, duration of nCPAP, duration of oxygen, culture positive sepsis, BPD, Intraventricular haemorrhages (IVH) grade ≥ 3. cystic periventricular leukomalacia (PVL), retinopathy of prematurity and mortality. Data will be collected until death or discharge from the hospital.

**Figure 1:** Clinical trial protocol for titration, weaning and removal of CPAP

[figure not shown]

Note: Titration will be done primarily based on clinical features and pulse oxygen saturation; arterial blood gas and chest X ray will be used for decision making wherever available

* <6 and >8 posterior intercostals spaces is defined as under and over inflation respectively, ^£^ICR: Intercostal Retractions

**Weaning of CPAP**: Weaning from CPAP will be attempted if the infant will have good respiratory efforts and will be free of apneas and bradycardia in the past 24 hours and if one or more of the following will be present:

1. Stable or decreasing oxygen requirement over the past 12 hours
2. Chest wall hyperinflated* (either clinically or in a Chest X ray) with absence of retractions and a pulmonary air leak ruled out.

Note: If the infant did not tolerate the decrease in CPAP, as judged by an increase in oxygen requirement by 15% more than that in the preceding 12 hours, the CPAP pressure will be again increased by1 cm of H_2_O.

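### The severity grade in the primary outcome is ordered, but the only rule for categorical outcomes ignores order, and the plan does not say whether severity is tested as grade or score

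*Protocol*

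**What the plan says.** Under OUTCOMES MEASURED the protocol states: "Incidence and severity of nasal injury is the primary outcome of the study". The primary objective names the same pair. The Scoring list under Table 1 turns a summed score into four ordered levels: 0 is no injury, then "1-4= mild injury", then "5-6= moderate injury", and 7 or more is severe.

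The Statistical analysis section gives one rule for this type of variable: "Categorical outcome variables will be analysed by Chi square test with continuity correction" or Fisher's exact test. It makes no exception for ordered grades and names no trend or ordinal test. A later sentence assigns Mann-Whitney U to variables with a skewed distribution. The significance threshold is a P value below 0.05.

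The sample size, under MATERIAL & METHODS, concerns injury yes/no: "Assuming an incidence of nasal injury of 50% among the control group at the removal of CPAP", with an effect size of 30%. No severity effect is planned, and no expected split of mild, moderate and severe injury is given.

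**The concern.** The trial asks whether rotating the interface lessens injury. That question has a direction, and the grade was built to express it. An unordered chi-square on four grades spreads the comparison of two groups over three degrees of freedom and treats mild, moderate and severe as interchangeable labels. A significant result then says only that the distributions differ. Its statistic has no sign, and it yields no effect estimate for a shift towards milder injury.

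The rule also does not fit the table it would be applied to. The continuity correction belongs to a 2x2 table, whereas severity has four levels and the trial has three groups.

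Two routes to a severity test are therefore open: the grade by chi-square or Fisher, or the score by a rank test. Nothing says which is primary. For a component of the primary outcome, that choice should not be left until the data are seen.

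**Working it through.** **1. The planning figure.** The protocol assumes 50% injury in controls. The 30% effect is read here as absolute, 50% to 20%. The calculator is described as "Sample size was estimated by using Compare k Proportions: 1- way ANOVA Pairwise test", so alpha is divided by three comparisons:

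n = [p1(1−p1) + p2(1−p2)] × ((z(1−0.05/6) + z(0.80)) / (p1−p2))²

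= (0.25 + 0.16) × ((2.394 + 0.842) / 0.30)² = 47.7, rounded up to 48.

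This matches the stated 48 per group. With one comparison the formula gives 36 and with two it gives 44. A relative 30% reduction (50% to 35%) gives 167 to 223. So the sample size implies alpha 0.05/3 = 0.0167, whereas the analysis section states 0.05. Both are carried below, with 48 per group (before attrition) and 55 (the enrolment target).

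**2. A severity scenario.** The protocol gives no grade split, so one is assumed: controls 50% none, 30% mild, 12% moderate, 8% severe. To lower incidence and severity together, multiply the odds of being at or below each grade by 4:

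- none: odds 0.50/0.50 = 1, becomes 4, so 4/5 = 80.0%
- none or mild: odds 0.80/0.20 = 4, becomes 16, so 16/17 = 94.1%
- none to moderate: odds 0.92/0.08 = 11.5, becomes 46, so 46/47 = 97.9%

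The rotation grades are then 80.0 / 14.1 / 3.8 / 2.1%. Any injury falls from 50% to 20%, the planning contrast.

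**3. Power for two groups.** These come from 40,000 simulated trials per row, comparing the Pearson chi-square on the 2x4 table (3 df) with the tie-corrected Mann-Whitney test:

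| n per group | alpha | chi-square | rank test | loss (points) |
|---|---|---|---|---|
| 48 | 0.0167 | 59.5% | 79.0% | 19.5 |
| 48 | 0.05 | 76.0% | 89.5% | 13.5 |
| 55 | 0.0167 | 67.6% | 84.4% | 16.8 |
| 55 | 0.05 | 82.2% | 92.8% | 10.6 |

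**4. Other assumed splits.** The splits of the injured 50% ran from mainly mild to equal thirds. The shift was either the odds ratio above or an unchanged severity mix among fewer injured infants.

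- Chi-square at 0.0167: loss of 16 to 20 points with 48 per group, 14 to 17 with 55.
- Chi-square at 0.05: 11 to 14 points with 48, 9 to 11 with 55.
- Fisher's exact test (two splits, 4,000 runs): 8 to 12 points at 0.05, 10 to 17 at 0.0167.
- All three groups at 0.05, with both single-interface groups at the control split: chi-square on 6 df loses 10 to 15 points against Kruskal-Wallis.

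The range over all of these is about 8 to 20 points.

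**5. A pattern that reverses the sign.** Hold any injury at 50% in both groups and move only the mix among the injured, from 50/20/15/15% to 50/40/7/3% (assumed). With 48 per group at 0.05, the chi-square has about 70% power and the rank test about 16%.

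**The case against.** **The direction of the power difference depends on the effect.** A change within the injured is what severity adds beyond incidence, and step 5 shows that the unordered test can win there. The pattern is not fanciful. The literature review cites a mask-versus-prongs trial of 72 neonates in which any-grade trauma was similar (RR 1.07) but grade II/III trauma was 0 versus 31%. That trial did not test rotation, so it does not show that chi-square is better here. It does rule out any general statement that the unordered test is weaker. This stands.

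**A reader might infer one figure, about 18 points lost at the planned effect.** The documents do not support that. A loss of that size needs an assumed grade split, a shift of the kind in steps 2 to 4, and alpha 0.0167, which the analysis section does not state. The planned effect concerns injury yes/no. For that endpoint the uncorrected 2x2 chi-square with 48 per group has about 77% power at 0.0167 and 88% at 0.05, close to the rank test in step 3. The loss applies only to the four-level grade.

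**Severity may already have a rank test.** The grade comes from a numeric total, the case record form collects total and maximum scores, and such a score is probably skewed. This stands in part. It makes the assignment ambiguous and does not remove the problem: the grade itself is categorical, the section does not choose between grade and score, and Mann-Whitney compares only two groups.

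**The chi-square is valid, and model choice belongs in an analysis plan.** Ignoring order causes no bias, and reported percentages would show the direction. But this is not a detail left open. The protocol has already fixed a rule for categorical outcomes, and that rule suits the grade poorly.

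**Conclusion.** The point holds in a limited form. Severity is part of the primary outcome and is an ordered grade. The only rule stated for categorical outcomes ignores that order and carries a correction that cannot apply to four levels. Whether severity is tested as grade or score is not settled.

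If rotation lowers incidence and severity together, the unordered test loses roughly 8 to 20 points of power against a rank test. That range rests on assumed severity splits, on any injury falling from 50% to 20%, on alpha 0.05 or 0.0167, and on 48 or 55 infants per group. If only the mix among the injured changes, the ordering of the tests can reverse.

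The trial's validity is not at stake, and neither is the power of the yes/no incidence comparison for which it was sized. The change is worth making because it gives a directional estimate, replaces a rule that does not fit the table, and fixes the test in advance at almost no cost.

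**What to change.** In the Statistical analysis section:

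- State that severity is analysed as the four-level grade by one prespecified ordinal method. Either use a proportional-odds model with group (three levels) and the gestation stratum, reporting common odds ratios for rotation versus mask and rotation versus prongs, or use Kruskal-Wallis followed by pairwise rank tests.
- Use the multiplicity level implied by the sample size for the pairwise comparisons (0.05/3).
- Report the count in each grade for each group, and check the proportional-odds assumption if that model is chosen, so that a change confined to the injured is visible.
- Keep a chi-square test for yes/no incidence, and limit any continuity correction to 2x2 tables.
- If the raw score is also compared by a rank test, label it supportive.

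The cost is a few sentences, with no extra data. The downside is some loss of power if only the severity mix among the injured changes.

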**Introduction**

Delivering Continuous Positive Airway Pressure (CPAP) has become the standard of respiratory care in neonates. Nasal CPAP remains an efficacious way of delivering CPAP in preterm neonates with respiratory distress^(1)^. With the increasing use of nasal CPAP, the safety and comfort associated with nasal CPAP has come into the forefront. The reported incidence of nasal injuries associated with use of CPAP is 20% to 60% ^(2-6)^ and range from simple blanching of the nasal tip to serious nasal septal necrosis and septal drop. These nasal injuries may lead to long-term consequences including cosmetic problems. Local pressure at the nasal interface compounded by the cutaneous vulnerability and certain anatomical peculiarities such as end-vascularization of the Columella and nostrils are the principle factors reported to be responsible for the nasal injuries^(7)^. Lower gestational age, lower birth weight and longer duration of CPAP and neonatal intensive care unit stay have been reported as risk factors for nasal injury^(3,6)^. Apart from these factors, type of nasal interface and CPAP delivery devices may be important determinants of nasal injury associated with nasal CPAP. In this study we plan to evaluate if rotation of nasal interface reduces the incidence of nasal injury in comparison to use of a single interface (prong or mask).

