**Methodology**

Enrolment and randomization process:

Eligible pregnant mothers at a gestational period of <=30weeks will be approached for an informed, written consent for participation in the study. Eligible infants will be stratified as per gestational age, viz. <28 weeks and 28^0/7^-30^6/7^weeks. Those who satisfied the inclusion and exclusion criteria after admission to the neonatal unit will be enrolled in the trial and will be randomly allocated to either mask or prong group.

A second randomization would be done to continue same interface or allocate to rotating group if the infant continues to be on the nasal CPAP after 8 hours of starting CPAP. Those randomized to rotating group will be subjected to mask interface if on prongs and those on prongs will be subjected to mask and the other group would continue with the same interface as before (Figure). Allocation will be done by a web based random number sequence generator ([www.randomization.com](http://www.randomization.com)). Separate person who is not involved in the study will generate the random sequence. Randomization will be stratified for gestation <28 weeks and 28 to 30 weeks. Allocations will be concealed by placing the allocation sequence in opaque, tamper proof, sealed, serially numbered envelopes. The nature of the intervention will prevent us from blinding of the intervention from the investigators as well as the treating team. However, the statistician and the neonatologist reviewing nasal injury images will be blinded from the study allocation details. Further attempts will be made to minimize the bias by maintaining a strict study protocol.

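### Randomisation is stratified by gestation but no planned test uses the strata; a stratified nasal-injury test would recover a few points of power if gestation is prognostic, at almost no cost

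*Protocol*

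**What the plan says.** - **Randomisation** (Protocol, Methodology, enrolment and randomization): "Randomization will be stratified for gestation <28 weeks and 28 to 30 weeks". The section describes a web-based sequence and sealed envelopes. It names no blocks, minimisation or other balancing device. There are two successive randomisations, the second only for infants still on CPAP after 8 hours.
- **Risk factors** (Protocol, Introduction): "Lower gestational age, lower birth weight and longer duration of CPAP and neonatal intensive care unit stay have been reported as risk factors" for nasal injury. Birth weight is recorded on the screening form in Annexure 1.
- **Tests** (Protocol, Statistical analysis): "Categorical outcome variables will be analysed by Chi square test with continuity correction" or Fisher's exact test. For other variables: "Normal distributed independent variables will be compared by repeated measures ANOVA test whereas a non-parametric test (Mann-Whitney U) will be used" when the distribution is skewed. The threshold is: "A P value of less than 0.05 will be considered significant". No stratified or covariate-adjusted analysis appears anywhere in the protocol.
- **Sample size** (Protocol, Material & Methods): "Assuming an incidence of nasal injury of 50% among the control group at the removal of CPAP", and "three group comparisons with an effect size of 30% with 80% power, alpha error of 5% the sample size calculated is 48 in each group", raised to 55 for 10% attrition.

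**The concern.** The design treats gestation as important enough to stratify on, but the analysis then sets it aside. If gestation predicts nasal injury, part of the variation in the outcome is explained by the stratum. A test that ignores the stratum counts that part as noise and loses power. If the groups are also balanced within strata, the true variance of the difference between groups is smaller than the crude test assumes, so the crude test rejects less often than its nominal level.

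The trial is small and sized at 80% power, so a few points matter. The same reasoning applies to secondary outcomes that may depend on gestation, such as CPAP and oxygen duration, BPD, IVH and mortality.

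**Working it through.** **1. The plan's own sample size.** Inputs: 50% control incidence, a 30% effect read as absolute (50% versus 20%), 80% power, two-sided alpha 0.05 (two-sidedness assumed), three pairwise comparisons.

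n = [pA(1−pA) + pB(1−pB)] × [(z(1−α/(2×3)) + z(0.80)) / (pA−pB)]², with pA = 0.50 and pB = 0.20, gives 47.7, so 48 per group. This reproduces the stated figure. With one comparison the formula gives 36. For attrition, 48/0.9 = 53.3, so 54; the stated 55 is just above.

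The 48 therefore implies a pairwise level of 0.05/3 = 0.0167, whereas the Statistical analysis section tests at 0.05. Results are shown at both levels.

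**2. Assumptions the protocol does not supply.** 40% of infants under 28 weeks; stratum odds ratio for injury of 1, 2, 4 or 6; the same treatment odds ratio in both strata; 48 evaluable infants in each of two groups compared pairwise.

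**3. Why the crude test can be conservative, by hand.** At a stratum odds ratio of 4, control risks are about 70% (under 28 weeks) and 37%, since 0.4×0.70 + 0.6×0.37 ≈ 0.50.

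- Variance the crude test uses: 0.50×0.50 = 0.25.
- Variance within strata: 0.4×0.70×0.30 + 0.6×0.37×0.63 = 0.084 + 0.140 = 0.224.
- Ratio of standard errors: √(0.224/0.25) ≈ 0.946.

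With exact balance, the crude cut-off of 1.96 acts like 1.96/0.946 ≈ 2.07, a true two-sided size of about 3.8%. Simulation gives about 4.0%. Without balance, chance imbalance puts the between-stratum variance back and the effect disappears.

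**4. Simulation.** The stratified statistic is Cochran-Mantel-Haenszel: (|Σ(aᵢ − Eᵢ)| − c)² / ΣVᵢ over the two strata, with c = 0.5 (continuity-corrected) or 0. Here aᵢ is the number injured in one group in stratum i, and Eᵢ and Vᵢ are its hypergeometric mean and variance.

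| Stratum odds ratio | Power change from stratifying, alpha 0.05 | Same, alpha 0.0167 | True size of crude test, nominal 5% |
|---|---|---|---|
| 1 | about 0 | about 0 | 5.2% |
| 2 | +1 point | +1 point | 4.8% |
| 4 | +3 points | +4 to 5 points | 4.0% |
| 6 | +4 points | +7 points | 3.4% |

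Power columns: 50% versus 20%, continuity correction on both tests, balanced strata. Size column: uncorrected, balanced strata.

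Without balance (simple allocation within strata) the power changes are similar, with a loss of up to about 1 point at odds ratio 1. The crude uncorrected size is then about 5.2% throughout.

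**5. Separating the continuity correction.** With no stratum effect, the correction alone takes size to about 3.1% and power for 50% versus 20% at 0.05 from 88% to 83%. At odds ratio 4 with balance, at 0.05:

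- crude, corrected: 84.1%
- stratified, corrected: 86.8%
- crude, uncorrected: 89.5%
- stratified, uncorrected: 91.2%

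Going from the first to the last gains 91.2 − 84.1 = 7.1 points. Of these, 89.5 − 84.1 = 5.4 come from dropping the correction and 91.2 − 89.5 = 1.7 from stratifying. The corrected stratified test still has size of only about 2.9%. Fisher's exact test, the stated alternative, was not simulated.

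**The case against.** **Covariates are usually left to the SAP.** That is often so, and the paragraph does not forbid adjusted analyses. But the protocol is not silent: it names the tests for all categorical outcomes, the primary one included, and they do not reflect its own randomisation. An SAP that followed this text would inherit the mismatch.

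**A reader might infer that the planned P values are simply too conservative.** The documents do not support that as a flat statement. It requires balance within strata, and the protocol names nothing that secures it. Two successive randomisations, the second among infants still on CPAP, followed by attrition, make exact balance in the final groups less certain still. Without balance the crude test keeps its level and only power is lost.

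Nor is the plan conservative overall. It states no multiplicity rule for three groups. If all three pairs are tested at 0.05, the chance of at least one false positive at odds ratio 4 with balance is about 9.8% uncorrected, or 5.9% with the correction. That is a separate matter.

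**Gestation may be only weakly prognostic.** The Review of Literature reports a prongs-versus-mask trial in very low birth weight infants in which only CPAP duration stayed significant after control for gestation and birth weight. This stands as a reason to expect a small gain. It is not decisive, because CPAP duration is measured after randomisation and may lie on the path from gestation to injury.

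**Birth weight was not used to stratify.** This is correct. Omitting it is not a mismatch with the randomisation and does not lower the error rate. Adjusting for it is an option for precision only.

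**Conclusion.** The point holds as a nearly free improvement, not as an error that invalidates the analysis. The crude tests remain valid and ignoring the strata does not inflate the false-positive rate.

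What is lost is power, conditional on gestation being prognostic: about 1 to 4 points at alpha 0.05, or 1 to 7 points at 0.0167, for stratum odds ratios of 2 to 6, and nothing if gestation has no effect. Conservatism of the crude test is a further consequence only where the strata are balanced.

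The direction of the power effect is secure. Its size rests on the assumed odds ratios and the assumed 40% share under 28 weeks, neither of which the protocol gives. The continuity correction costs more than ignoring the strata does at odds ratios of 2 to 4, and needs its own remedy.

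**What to change.** In the Statistical analysis section of the protocol:

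- Make the primary nasal-injury comparison a Cochran-Mantel-Haenszel test stratified by the gestation stratum used at randomisation, without continuity correction. Alternatively, use logistic regression with group and stratum; birth weight may be added as a prespecified covariate, for precision only.
- Report the adjusted effect with a 95% confidence interval.
- Use stratum-adjusted analyses for the secondary outcomes.
- Keep the crude test as a sensitivity analysis.
- Do not adjust for CPAP duration, which is measured after randomisation.

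In the Methodology section, state whether allocation is blocked within strata.

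The cost is a few sentences. Gestation and birth weight are already recorded, and no further infants or data are needed. The statistical downside is up to about 1 point of power if gestation turns out to have no effect on nasal injury.

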**Secondary objectives**

To compare the following among the groups (prongs vs. masks vs. rotation of mask and prongs)

- The need for mechanical ventilation.
- The duration of CPAP, oxygen and ventilation
- Incidence of bronchopulmonary dysplasia as defined by requirement of oxygen or any form of respiratory support till 28 days of life (BPD)
- Ventilator associated pneumonia (VAP) as per NEO-KISS criteria
- Intraventricular haemorrhages (IVH) as defined by Papille et al.
- Periventricular leucomalacia (PVL) at discharge according to de Vries criteria
- Mortality among the groups will be noted till the baby is in NICU

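### The tests named in the protocol do not fit three independent groups, and its analysis threshold (0.05) differs from the per-comparison level (0.0167) that the sample size implies

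*Protocol*

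**What the plan says.** The Statistical analysis section of the protocol gives one rule for each type of variable.

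- Categorical: "Categorical outcome variables will be analysed by Chi square test with continuity correction", with Fisher's exact test as the alternative.
- Continuous: "Normal distributed independent variables will be compared by repeated measures ANOVA test whereas a non-parametric test (Mann-Whitney U) will be used" when the distribution is skewed.
- Threshold: p below 0.05. No adjustment for multiple comparisons is stated.

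The design has three arms of different infants: continued prongs, continued mask, and rotation. The secondary objectives are "To compare the following among the groups (prongs vs. masks vs. rotation of mask and prongs"), and they include durations of CPAP, oxygen and ventilation. The primary outcome, incidence and severity of nasal injury, is assessed six hours after CPAP is removed (Outcomes measured).

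The sample-size paragraph in Material & Methods starts from "Assuming an incidence of nasal injury of 50% among the control group at the removal of CPAP". It continues "Assuming three group comparisons with an effect size of 30% with 80% power", and with an "alpha error of 5% the sample size calculated is 48 in each group", raised to 55 for 10% attrition. The method it names is a pairwise comparison of k proportions.

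**The concern.** Each named test needs a data structure that this trial does not have for the outcomes in question.

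- **Repeated-measures ANOVA** needs several measurements on the same infant. Duration of CPAP or oxygen is one value per infant, so there is no within-infant factor to model.
- **Mann-Whitney U** compares two samples. With three arms it gives no overall test, and the protocol sets out no scheme of pairs. Durations of respiratory support are likely to be skewed, so this would probably be the working test for them.
- **The continuity correction** belongs to the 2x2 table. It is not defined for injury by three groups, nor for the four severity grades by three groups.

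An analyst therefore has to choose substitutes, possibly with data in hand.

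There is a second problem. If the primary outcome is instead tested pair by pair, so that the correction does apply, power and error control depend on the per-pair significance level. The sample-size paragraph and the analysis section imply different levels.

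**Working it through.** **Inputs.** Control rate 50%, effect 30%, power 80%, alpha 5%, three comparisons, 48 per group before attrition and 55 after (all from Material & Methods); threshold 0.05 at analysis (Statistical analysis). Assumed because not stated: two-sided tests, an absolute effect of 30 points (50% versus 20%), equal groups, and any injury yes/no as the endpoint.

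**Step 1: reproduce the 48.** The pairwise formula for k proportions is

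n = [p1(1−p1) + p2(1−p2)] × [(z(1−α/(2τ)) + z(0.80)) / (p1−p2)]², where τ is the number of comparisons.

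- Variance term: 0.5×0.5 + 0.2×0.8 = 0.41.
- τ = 3: z(1−0.05/6) = 2.394 and z(0.80) = 0.842, so n = 0.41 × (3.236/0.30)² = 47.7, rounded up to 48.
- τ = 1 gives 35.8 (36) and τ = 2 gives 43.3 (44).
- Reading the 30% as relative (50% versus 35%) gives 167 (τ = 1) to 223 (τ = 3).

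Of these readings, only an absolute effect with alpha divided by three gives 48. The design level per pair is therefore 0.05/3 = 0.0167. For attrition, 48/0.9 = 53.3, so 54; the stated 55 is close.

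**Step 2: exact power of the pairwise tests, 50% versus 20%.** All pairs of binomial counts were enumerated.

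| Per-pair level | n per group | Pearson, uncorrected | Continuity-corrected | Fisher |
|---|---|---|---|---|
| 0.05 | 48 | 88.5% | 83.1% | 83.1% |
| 0.05 | 55 | 92.6% | 89.1% | 89.1% |
| 0.0167 | 48 | 77.4% | 69.4% | 70.9% |
| 0.0167 | 55 | 83.5% | 77.3% | 78.3% |

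At 0.0167 and 48 per group, the shortfall from 80% is 80 − 69.4 = 10.6 points. The correction accounts for 77.4 − 69.4 = 8.0 of them. The remaining 2.6 come from the unpooled-variance sample-size formula, because the uncorrected test also falls short there.

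**Step 3: overall error with three pairwise tests at 0.05.** These figures are simulated with no difference between groups.

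- Mann-Whitney U: about 12% chance of at least one false positive.
- Continuity-corrected chi-square, common rate 50%: 7% to 8%.
- Uncorrected chi-square, same rate: 11% to 13%.

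**Step 4: the overall three-group test.** An uncorrected 3x2 chi-square at 0.05 with 48 per group has about 91% power for true rates of 50/50/20 and 81% for 50/35/20 (simulated). This answers whether any group differs, not which pair does.

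**The case against.** A reader might infer that the continuity correction by itself takes the primary comparison below its planned 80% power. The protocol does not support that. The only analysis threshold it states is 0.05, and there the corrected test and Fisher's test both keep 83% at 48 per group and 89% at 55. The shortfall needs the 0.0167 level, which is inferred from the sample-size calculation and is not written in the analysis section. Even at that level, part of the loss at 48 per group is not due to the correction. This objection stands, so the power figures here are conditional.

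The 12% error and the 69% power also cannot both be held against the plan. The first belongs to testing at 0.05 and the second to testing at 0.0167. That stands too.

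The ANOVA and Mann-Whitney errors fall mainly on secondary outcomes. Incidence and graded severity can both go under the categorical rule, and Fisher's test extends to a three-group table. This is fair, and it lowers the severity.

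Finally, repeated-measures ANOVA could have a proper use. The nasal-injury monitoring chart records scores on days 1 to 7, 14, 21, 28 and at discharge, and the literature review describes an earlier rotation trial analysed with that method. But the analysis section does not tie the method to those scores, so the text still needs correcting.

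**Conclusion.** The point holds as a mismatch between named tests and design, and as an inconsistency between two significance levels. Repeated-measures ANOVA, Mann-Whitney U and the continuity correction are not three-group tests for outcomes measured once per infant. This follows from the protocol's own text and needs no assumption.

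The numerical part depends on the level used per pair. At 0.05, the named pairwise tests reach the planned power but do not hold the overall error at 5%. At 0.0167, the level behind the 48, the continuity-corrected test has 69% to 77% power and misses the plan, while the uncorrected test has 77% to 83.5%. These figures rest on two-sided tests, 50% versus 20%, equal groups and a binary injury endpoint.

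Severity: should-fix. The plainest errors mainly affect secondary outcomes, and at the stated 0.05 no loss of power below 80% is shown for the primary comparison.

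**What to change.** Rewrite the Statistical analysis section as follows.

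1. Categorical outcomes, including injury: three-group Pearson chi-square (3x2 or 3xk) without continuity correction; Fisher-Freeman-Halton if expected counts are small.
2. Normally distributed outcomes measured once: one-way ANOVA.
3. Skewed durations and the ordinal injury score: Kruskal-Wallis.
4. Pairwise follow-up with uncorrected tests at a stated level that agrees with the sample-size paragraph: 0.05/3, or another named family-wise procedure.
5. Keep a repeated-measures method only if it is tied explicitly to the serial nasal scores in the monitoring chart.

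State power for the chosen pairwise test and level. With the uncorrected test at 0.0167, exact power is 79.3% at 50 evaluable infants per group and 80.5% at 51, so the planned 80% depends on how many of the 55 are analysed.

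The cost is wording only: no change to recruitment, data collection or conduct, and the replacement tests are standard procedures in the planned software. The change should be made before any outcome data are examined by group.
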